### Evidence-based antibiotic stewardship interventions

#### EOS calculator

The EOS calculator, which was developed by researchers of Kaiser Permanente, is applicable to neonates born at 34 weeks of gestation or later and can be used within the first 24 hours after birth.^10^ In this implementation project, it is advised to apply the EOS calculator to all neonates with increased risk of EOS, based on the presence of at least one risk factor or clinical symptom as specified in the current Dutch Society of Paediatrics’ guideline ‘Prevention and treatment of early onset neonatal infections’.^21^ The EOS calculator uses information on regional incidence and five maternal factors combined with the clinical evaluation of the neonate to assess individual EOS risk. The calculator then provides recommendations on the need for clinical observation using repeated evaluation of vital parameters, a blood culture and start of empirical intravenous antibiotics. In line with the protocol of the Dutch randomised controlled trial on EOS calculator safety and effectiveness, some deviations or clarifications have been made to the original EOS calculator’s approach in this study’s clinical protocol.^29^ First, the EOS calculator’s recommendation to obtain a blood culture and perform clinical observations is replaced with clinical observations only. This deviation reflects usual practices in the Netherlands, where obtaining a blood culture without subsequent antibiotic administration is uncommon. Second, evaluation of vital parameters is done every 3 hours instead of 4 hours, according to current Dutch workflows. Third, the EOS calculator gives no specific timeframe for observations in the ‘routine vitals’ recommendation, which is up to own interpretation. In this study’s clinical protocol, the duration has been standardised at 24 hours. For this implementation project, the EOS calculator is chosen over a 48-hour serial clinical examination approach, that also has the potential to significantly reduce antibiotic prescriptions, but demands more resources.^30^ The decision was based on the EOS calculator’s stronger evidence for reducing unnecessary antibiotic use, as well as logistical considerations regarding the demand for more staff and room capacity due to longer duration of the observation period of serial clinical examinations.

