#### Data from the electronic health record

Data will be collected using automated data extraction methods of the hospitals’ business intelligence unit. Data will be sampled from all neonates with suspected EOS who were started on antibiotics during the pre- and post implementation period and include gestational age, birth weight, initiation of antibiotic treatment within the first 3 days of life, names and dosages of antibiotics used, duration of antibiotic treatment, blood culture results with pathogen identification, CRP and procalcitonin values within the first 28 days of life, readmissions within 28 days after discharge, re-initiation of antibiotic therapy within 28 days and discharge destination (home or transfer to another hospital). Additionally, the total number of live births during both periods will be obtained from hospital registries. All data will be securely stored in the Castor Electronic Data Capture (EDC) system.

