### Analysis

#### Primary outcome

An ITS analysis will be conducted to compare trend of overall DOT (all types of antibiotic agents) per 1000 live births pre- and post-intervention. The ITS will have at least four data points in the pre-implementation period and four datapoints in the post implementation period, based on quarterly intervals. If the number of cases allows dividing the data into more datapoints, this may be considered. To account for potential clustering of observations within hospitals and potential differences between hospitals, we will apply a mixed-effects segmented regression analysis for ITS (‘joinpoint regression’) with DOT as dependent variable and random intercept for each hospital. Also, we will include random slopes for the post-intervention trend, allowing hospitals to differ not only in baseline DOT levels but also in how they respond to the implementation. Fixed effects include intervention phase (pre/post) and segmented time after the intervention to estimate both immediate level changes and changes in trend. Confounders, including the number of positive blood cultures, mean gestational age and mean birth weight will be included as time-varying covariates. Depending on data availability, we may also examine trends during the intermediate implementation phase to explore changes during this transition period as secondary analysis. Autocorrelation of residuals will be checked by using the Durbin-Watson test, and if present, corrected. Results will be reported as adjusted changes in level and trend, with 95%CIs, reflecting both pooled effects and between-hospital variability. Additionally, a before-after comparison will be performed using a t-test or Mann-Whitney U test, for both overall DOT and DOT per individual antibiotic agent.

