#### Sample size

Estimating the median DOTs in the Netherlands during the pre-implementation period is challenging due to the lack of data on the exact duration of antibiotic treatment for EOS in Dutch neonates. However, a mean antibiotic initiation rate of 3.8% of all live-born neonates was reported in 13 secondary Dutch hospitals.^40^ Additionally, another study among Dutch hospitals found that antibiotics were continued intravenously for more than 72 hours in 31.5% of cases in.^41^ Since neonates in the Netherlands are usually treated for either 24–72 hours (average 2 days) or 7 days, we can estimate the pre-implementation DOTs to be 136 per 1000 live-births (calculated as follows: (0.685×38 neonates×2 days) + (0.315×38 neonates×7 days)). This estimate matches the mean antibiotic exposure in other high-income countries, which is 135 (range 54–491) DOTs per 1000 live births as reported in the AENEAS study.^1^ Our goal for the post implementation period is to reduce the antibiotic initiation rate to 2% and halve the number of full treatment courses, aiming for 60 DOTs per 1000 live-births. However, we consider a reduction of at least 10% of DOTs to be clinically relevant. This would result in a post implementation outcome of 121.5 DOTs per 1000 live-births. Assuming a power of 90% and an alpha of 5%, a sample size of 2790 (1395 per group) would be required. This sample size will be feasible for both the total study population and most individual sites, since Dutch hospitals typically report annual birth rates ranging from 1000 to 3500, averaging approximately 2500 births per hospital per year. However, in hospitals with already low pre-implementation DOTs, no differences in absolute DOTS or trends may be found. This is acceptable, as this would demonstrate that these hospitals are already leading in the reduction of antibiotic use, and finding a difference through greater sample size would not be clinically relevant.

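### The primary interrupted time series adjusts for gestational age and birth weight of treated neonates, a group the EOS calculator is meant to change, so the estimated effect can be attenuated

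*Protocol article*

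**What the plan says.** Under Analysis, Primary outcome, the protocol article plans a mixed-effects segmented regression to "compare trend of overall DOT (all types of antibiotic agents) per 1000 live births pre- and post-intervention". The covariates are fixed there: "Confounders, including the number of positive blood cultures, mean gestational age and mean birth weight will be included as time-varying covariates". The results to be reported are the adjusted changes in level and trend, so these covariates are part of the headline estimate. The same section adds an unadjusted before-after test.

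Under Data from the electronic health record, gestational age, birth weight and culture results are listed as patient-level items, with this scope: "Data will be sampled from all neonates with suspected EOS who were started on antibiotics during the pre- and post implementation period". For all births the section names one item: "the total number of live births during both periods will be obtained from hospital registries".

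Under EOS calculator, the calculator's "recommendation to obtain a blood culture and perform clinical observations is replaced with clinical observations only", because in the Netherlands "obtaining a blood culture without subsequent antibiotic administration is uncommon".

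Under Sample size, "a mean antibiotic initiation rate of 3.8% of all live-born neonates was reported in 13 secondary Dutch hospitals", and the goal after implementation is 2%.

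**The concern.** The outcome has all live births as its denominator. The two means, as far as the stated data source allows, have only treated neonates as theirs. The calculator decides who is treated. If it spares term neonates more often than late-preterm ones, mean gestational age and birth weight of those still treated will fall because of the intervention. A model that holds these means constant then credits part of the effect to the covariates.

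A true confounder here would be a change in the case mix of births between 2023 and the post-implementation year. The treated-only mean mixes any such change with the effect of the calculator.

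The number of positive cultures raises a smaller issue. It is a count set against a rate, so it scales with hospital size. Since cultures accompany antibiotic starts, its contaminant part falls when starts fall. What is at stake is the size of the primary level and trend change.

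**Working it through.** **1. How far the treated group changes.** The plan's baseline reproduces: 0.685 x 38 x 2 + 0.315 x 38 x 7 = 52.06 + 83.79 = 135.85, stated as 136 DOT per 1000. The target cuts starts by (3.8 - 2)/3.8 = 47%. At the stated average of 2500 births per hospital-year there are 625 births per quarter. The means then rest on 625 x 0.038 = 23.75 treated neonates before and 625 x 0.02 = 12.5 after.

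**2. Whether the mean can shift.** The documents give no case-mix figures. Assume 6% late-preterm births with 16% of them treated, true EOS in 0.05% of births, and mean gestational age 39.6 weeks (term) and 35.7 weeks (late preterm).
- Term starts are 0.038 - 0.06 x 0.16 = 0.0284 of births and late-preterm starts 0.0096.
- Before: (0.0289 x 39.6 + 0.0096 x 35.7)/0.0385 = 38.63 weeks (0.0289 includes EOS).
- After, if only term starts fall, to 35% of their former rate: 0.0284 x 0.35 = 0.00994, plus EOS = 0.01044. Then (0.01044 x 39.6 + 0.0096 x 35.7)/0.02004 = 37.73 weeks.
- If both groups fall by the same proportion, the mean hardly moves.

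**3. What adjustment does.** Simulation of 11 hospitals x 8 quarters, 400 runs per scenario, hospital fixed effects in place of the planned random effects, separate slopes before and after. Contamination was 1% of treated neonates unless stated. The effect is the post-minus-pre contrast in mean DOT per 1000.

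| Scenario | Unadjusted | All three covariates | Ratio |
|---|---|---|---|
| No bundle effect | -0.9 | -0.8 | n/a |
| Uniform cut, hospitals alike | -82.7 | -81.4 | 0.98 |
| Term-only cut, hospitals alike | -82.8 | -83.1 | 1.00 |
| Mainly late-preterm cut, hospitals alike | -82.0 | -80.1 | 0.98 |
| Uniform cut, hospitals differ, 3% contamination | -79.9 | -76.1 | 0.95 |
| Term-only cut, hospitals alike, term starts swing by quarter | -84.9 | -78.3 | 0.92 |
| Small term-only cut, hospitals differ, swings | -15.5 | -13.8 | 0.89 |
| Term-only cut, hospitals differ | -78.6 | -66.3 | 0.84 |
| Term-only cut, hospitals differ, swings | -80.5 | -62.7 | 0.78 |

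A second set of 200 runs per scenario (7% late preterm, term starts cut 40-50%, late-preterm starts 0-20%) gave losses of 1 to 14%, for example -58.4 against -50.1.

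**4. Why the loss varies.** Approximately, adjusted effect = unadjusted effect - sum of (covariate coefficient x shift in that covariate). Birth weight is left out below because its fitted coefficient rounds to zero.
- Term-only cut, hospitals differ: gestational age 9.52 x (37.51 - 38.63) = -10.7; cultures 12.14 x (0.39 - 0.49) = -1.2. Then -78.6 + 11.9 = -66.7, against the fitted -66.3.
- Term-only cut, hospitals alike: gestational age -1.725 x (37.74 - 38.63) = +1.5; cultures 11.853 x (0.39 - 0.50) = -1.3. Then -82.8 - 1.5 + 1.3 = -83.0, against -83.1.
- Uniform cut, 3% contamination: gestational age about 0; cultures 12.05 x (0.62 - 0.93) = -3.7. Then -79.9 + 3.7 = -76.2, against -76.1.

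A loss through gestational age therefore needs two things together: a shift in the mean, and an association of that mean with DOT across hospital-quarters. The second appears when hospitals respond unequally or term prescribing fluctuates.

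**The case against.** **The population of the means is not named.** The analysis section does not say over whom they are taken, and the outcome supplement and any SAP are not shown. This stands: the treated-only reading is an inference from the only stated source. If the full plan uses all births, the point on gestational age and birth weight falls away.

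**Only one component changes who is treated.** PCT-guided therapy and the oral switch act after antibiotics have started. This stands and narrows the mechanism to the calculator.

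**Positive cultures are a reasonable covariate.** A reader might infer that all three covariates are products of the intervention. The documents do not support that for cultures. True culture-proven EOS is largely not caused by the bundle. It raises DOT directly, since the PCT-guided therapy section sets at least 7 days of treatment, and it can differ by chance between periods. The observation-only rule keeps usual Dutch practice and adds no new restriction on culturing. Only the raw count and the contaminants remain open to criticism.

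**The before-after test is free of the problem.** It is, but it ignores trend and clustering by hospital, so it cannot stand in for the time series.

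**Precision.** A reader might add that three covariates are too many for 8 points per hospital. The plan fits one pooled model of about 11 x 8 = 88 hospital-quarters. In the simulations the run-to-run SD rose in some scenarios (7.8 to 10.0) and fell in others (13.7 to 13.2), so no general loss of precision is shown.

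**Conclusion.** The concern holds in a limited form. Mean gestational age and birth weight of treated neonates are post-intervention variables and should not be labelled confounders of DOT per 1000 live births. Adjusting for them can attenuate the primary estimate. Across simulations with assumed case mix, and with cultures also in the model, the loss was about 0 to 22%. Gestational age and birth weight contributed about nothing when starts fell uniformly.

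A reader might conclude that the adjusted result is biased. The documents do not show that, because they give no gestational age, birth weight or contamination figures. With no bundle effect there was no bias, so this route did not create a false claim of benefit. Nor should a loss of 12 to 18 DOT from an effect near 80 be set against the plan's relevance threshold of 13.5: the adjusted effects of 66.3 and 62.7 remain far above it. Near the threshold the loss was 15.5 - 13.8 = 1.7 DOT.

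**What to change.** Make the time series without treated-only gestational age and birth weight the primary estimate, and state in the text over which neonates any covariate is computed. If case-mix adjustment is wanted, use mean gestational age and birth weight, or the share born at 34-36 weeks, among all live births of at least 34 weeks from hospital birth registries. The bundle acts after birth and cannot change these. In the six simulated scenarios with like hospitals, adjusting for all-birth gestational age moved the effect by at most 0.1 DOT. Treated-only adjustment also did little harm there, so the case for the all-birth version rests on the reasoning more than on those runs.

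If cultures are kept, enter culture-proven EOS, contaminants excluded, per 1000 live births. Show the treated-only adjustment as a sensitivity analysis at most. Settle this before outcome data are analysed, so that the choice between estimates does not depend on them.

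Cost: model wording and, if adjustment is kept, one registry aggregate per hospital and quarter.

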#### Secondary outcomes

Quantitative data: Continuous data will be reported as mean with SD if normally distributed or as median with IQR if not normally distributed. Ordinal data, such as Likert scale responses, will be reported as medians with IQR. Other categorical data will be presented as frequencies with percentages with 95% CI where relevant. For comparisons between groups (pre-implementation and post implementation), continuous data will be analysed using an independent t-test if normally distributed or a Mann-Whitney U-test if not. Ordinal data will be compared using the Mann-Whitney U test, and other categorical data will be analysed using a χ^2^ test or Fisher’s exact test for small sample sizes. P values <0.05 will be considered statistically significant. All analyses will account for differences in group sizes where applicable.

Qualitative data: Transcripts of focus group evaluation sessions and interviews, field notes and open-ended survey questions will be analysed using a deductive analysis approach (directed content analysis). The first three evaluation sessions and interviews transcripts, as well as field notes and surveys, will be coded separately by two researchers, then compared and discussed to create consensus about codes. Subsequent transcripts, field notes and answers to open-ended questions will be coded by one researcher and discussed with the team in case of ambiguity. The data analysis will be an iterative process, with the analysis of the evaluation session or interview occurring before the following one.

For the implementation outcomes, data will be integrated following a convergent quantitative design, by combining quantitative data from the EHR, logbook and structured questionnaires with qualitative data from semi-structured interviews and field notes.^39^ This integration will allow us to gain a richer understanding of the adoption, fidelity, acceptability and feasibility of the antibiotic stewardship interventions, along with the fidelity to and appropriateness of the implementation strategies.

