#### Secondary outcomes—clinical

We will determine the proportion of neonates starting on antibiotics per 100 live births, proportion of neonates receiving antibiotics per predefined category of duration (36 hours, 36–48 hours, 48–72 hours, >5 days and >7 days), duration of therapy, proportion of neonates receiving IV-to-oral switch therapy, duration of hospital stay, cumulative number of laboratory tests, cumulative readmission rate within 28 days after birth, cumulative bacterial (re)infection rate within 28 days after birth, incidence of culture-proven EOS per 1000 live births, pathogen determination and antibiotic susceptibility and infection-related mortality within 28 days after birth. For all (re)infections, we will provide exact data on timing of the infection within the first 28 days as well as the pathogen determination.

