#### Surveys

All paediatricians of the participating sites will be invited to complete a survey both before and 1 year after the active implementation period to assess changes in knowledge and practice gaps and the adoption of the interventions. Additionally, the post implementation survey will evaluate fidelity to and appropriateness of the implementation strategies 1–3 and 8 and assess acceptability and feasibility of the antibiotic stewardship interventions (onlinesupplemental files 4  5). Paediatric residents will only take part in the post implementation survey, as their frequent rotations across different workplaces make pre-implementation comparisons unfeasible. Neonatology nurses will also be invited to complete a survey, specifically to assess the acceptability and feasibility of IV-to-oral switch therapy and the fidelity to and appropriateness of strategies 1, 6 and 7 (online supplemental file 6). All surveys will be distributed via the Castor EDC system.

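### Pre/post secondary comparisons use independent-sample tests that ignore the 11 hospitals supplying both periods; if hospital practice varies by period, p-values for the commoner clinical outcomes are too small

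*Protocol article*

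**What the plan says.** Under Analysis, Secondary outcomes, the protocol article names a test for each data type in the comparison of pre- with post-implementation:

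- Continuous: "continuous data will be analysed using an independent t-test if normally distributed or a Mann-Whitney U-test if not".
- Ordinal: "Ordinal data will be compared using the Mann-Whitney U test".
- Categorical: "other categorical data will be analysed using a χ^2^ test or Fisher’s exact test for small sample sizes".

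The threshold is "P values <0.05 will be considered statistically significant", and the only adjustment named is "All analyses will account for differences in group sizes where applicable". Neither hospital nor respondent enters any of these analyses.

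Under Analysis, Primary outcome, the interrupted time series has a random intercept per hospital and random slopes for the post-intervention trend. The stated purpose is "To account for potential clustering of observations within hospitals and potential differences between hospitals". The same section adds a before-after comparison of days on therapy by t-test or Mann-Whitney, again without a hospital term.

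Under Surveys, "All paediatricians of the participating sites will be invited to complete a survey both before and 1 year after the active implementation period", the purpose being to assess change. Residents answer only the post-implementation survey.

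**The concern.** The 12 months before and the 12 months after come from the same 11 hospitals. Two kinds of dependence follow, and they act in opposite directions.

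- Stable differences between hospitals appear in both periods and largely cancel in the comparison. Ignoring them costs a little efficiency.
- Shifts specific to a hospital and a period (staffing, local habits, case mix, uneven uptake) do not cancel. With 11 hospitals they average out slowly, and a test that counts neonates as independent does not see them. Its p-values are then too small and its confidence intervals too narrow.

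The outcomes affected include the start rate, duration of therapy, length of stay and 28-day readmission. Several of these will be read as evidence of effect or of safety.

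For the survey, a paediatrician who answers twice contributes two correlated answers. Treating them as coming from two people overstates the variance of the change, so a real change in knowledge or practice may be missed.

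**Working it through.** The protocol gives no power or error figure for secondary outcomes, so there is no stated figure to reproduce. Its sample size of 2790 concerns days on therapy and does not enter here.

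**Inputs from the protocol (Study setting; Sample size).** 11 hospitals; 1000–3500 births per hospital per year, about 2500 on average; start rate 3.8%. Treated neonates per hospital-period: 2500 × 0.038 = 95.

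**Assumed, because the protocol gives no values.** The hospital-by-period coefficient of variation (CV); the intraclass correlation (ICC); the between-period correlation of hospital effects (CAC); the within-person survey correlation r. Tests are taken as two-sided at 5%.

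If D is the true variance of the difference divided by the variance the test assumes, the true level is 2 × [1 − Φ(1.96/√D)].

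**1. Start rate per birth.** With m births per hospital-period and rate p, D ≈ 1 + m·p·CV² = 1 + 95·CV².

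| CV | D | True level |
|---|---|---|
| 10% | 1.95 | 16% |
| 20% | 4.80 | 37% |
| 30% | 9.55 | 53% |

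Simulating the χ² test with 11 hospitals of 1000–3500 births and no true average change gave 17–18%, 37–40% and 52–54% over repeated runs, and about 5% at CV 0. A paired t-test on hospital-level log rates stayed at 5–6%.

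**2. Outcomes among treated neonates, m = 95.** D = 1 + (m − 1)·ICC − m·ICC·CAC.

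- ICC 0.02, CAC 0.9: 1 + 1.88 − 1.71 = 1.17, level 7.0%.
- ICC 0.05, CAC 0.8: 1 + 4.70 − 3.80 = 1.90, level 15.5%.
- CAC 1 (stable hospital differences only): D = 1 − ICC, that is 0.98 or 0.95, level 4.8% or 4.4%.

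Simulated t-tests gave 7.0% to 14.7% over ICC 0.02–0.05 and CAC 0.8–0.9. A paired test on hospital-level differences held 4.4–5.3%.

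**3. Rare outcomes.** With an assumed 5 events per hospital-period, D = 1 + 5·CV². At CV 20% this is 1.20, level about 7%. At CV 10% it is 1.05, level about 5.6%.

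**4. Survey, if the same people answer twice.** Here D = 1 − r. For r = 0.3, 0.5 and 0.7 the true level is 1.9%, 0.6% and 0.03%. With 100 respondents to both rounds, a shift of 0.3 SD and r = 0.5 (all assumed):

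- Independent test: 0.3/√(2/100) = 2.12, and (2.12 − 1.96)/√0.5 = 0.23, power 59%.
- Paired test: 0.3/√(2 × 0.5/100) = 3.00, and 3.00 − 1.96 = 1.04, power 85%.

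**The case against.** **Direction.** A reader might infer that all clinical p-values are too small. The documents do not support that. Inflation needs variation by hospital and period, and the protocol gives no size for it. The random slopes in the primary model show that the authors expect hospitals to respond differently; they do not quantify drift in the absence of an effect. With stable hospital differences only, the planned tests are slightly conservative. The high figures belong to the per-birth start rate and do not transfer to treated-neonate or rare outcomes. All of this stands, and the point is therefore conditional.

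**Survey.** A reader might infer that the survey is a paired sample analysed wrongly. The protocol says only that all paediatricians are invited twice. Overlap and linkage are not stated, and without linkage no paired analysis is possible. The study ends in June 2026 after a 12-month post period and the article is dated November 2025, so the baseline survey has probably been collected already. A new linking code may come too late.

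**Duration classes.** A reader might also object that the classes "36 hours, 36–48 hours, 48–72 hours, >5 days and >7 days" leave a gap after 72 hours and overlap above 5 days, so that a χ² test across them is invalid. The protocol prescribes no single test across the classes, and each proportion can be compared separately. Reading the first class as up to 36 hours, the share beyond 72 hours and every intermediate class follow by subtraction. The exact definitions are in supplementary table S5, which is not shown. This is not part of the point.

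**Left to an analysis plan.** The tests are named in the article, so this is a stated method and not an omitted detail.

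**Conclusion.** The point holds in conditional form. The protocol recognises hospital clustering and uneven hospital response for its primary model, then fixes tests for the secondary comparisons that allow for neither. If hospital practice varies by period, the true level for the start rate is about 17%, 37% or 54% at a CV of 10%, 20% or 30%, and about 7–15% for outcomes among treated neonates. Both ranges rest on assumed variance components; simulation error and the approximation move the first set by two or three percentage points. For rare events such as infection-related death the effect is small.

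The supplementary before-after comparison of days on therapy has the same omission. The interrupted time series itself is not affected by this point.

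For the survey, the independent test is conservative to the extent that respondents overlap and their answers are positively correlated. How far cannot be determined from the protocol.

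**What to change.** - **Commoner clinical secondary outcomes, and the before-after comparison of days on therapy:** use paired hospital-level summaries, or mixed models with hospital and hospital-by-period effects and a small-cluster correction suited to 11 hospitals.
- **Very rare events:** keep exact or descriptive methods, since a mixed model may not be estimable.
- **Paediatrician survey:** where the two responses can be linked, use a respondent random-effect model, which also uses those who answered once, or Wilcoxon signed-rank or McNemar for those with both. Where they cannot be linked, state that the independent test is conservative for overlapping respondents. First check whether the survey system kept identifiers from the baseline round.

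For the clinical outcomes this is a change of analysis wording only and needs no new data. The price is wider confidence intervals. For the survey, the cost depends on whether linkage is still possible.

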**Methods and analysis:**

We will conduct a multicentre, prospective implementation study with interrupted time series and before-after analyses at the paediatric or specialised neonatal departments of 11 Dutch secondary hospitals and their surrounding neonatal care networks. A multimodal implementation strategy, designed using Implementation Mapping, is employed to facilitate implementation. The study population is twofold: (1) neonates born at 34 weeks of gestation or later with suspected EOS that will receive intervention-related care and (2) paediatricians, paediatric residents, neonatal nurses, maternity nurses and parents who are the focus of the implementation strategies. The primary outcome is days of antibiotic therapy per 1000 live-born neonates, which will be evaluated using interrupted time series analysis as well as before-after comparison. Secondary clinical outcomes will be assessed by comparing clinical data from the 12 months pre-implementation and post implementation. Implementation outcomes are adoption, fidelity, feasibility and acceptability of the interventions and fidelity and appropriateness of the implementation strategies. Implementation outcomes will be assessed using both qualitative and quantitative methods, including surveys, individual interviews and focus group interviews. A mixed-methods approach will be used to integrate clinical and implementation outcomes.

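### The rare harm outcomes are compared between periods by a p<0.05 test alone; the pre/post difference and ratio should be reported with 95% CIs, and a non-significant test should not be read as absence of harm

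*Protocol article*

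**What the plan says.** The section on secondary clinical outcomes lists "cumulative readmission rate within 28 days after birth, cumulative bacterial (re)infection rate within 28 days after birth, incidence of culture-proven EOS per 1000 live births" and "infection-related mortality within 28 days after birth". The abstract says how they will be assessed: "Secondary clinical outcomes will be assessed by comparing clinical data from the 12 months pre-implementation and post implementation".

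The analysis section for secondary outcomes treats them like any other categorical variable. For description: "Other categorical data will be presented as frequencies with percentages with 95% CI where relevant". For the comparison of periods: "other categorical data will be analysed using a χ^2^ test or Fisher’s exact test for small sample sizes". The decision rule for all secondary outcomes is "P values <0.05 will be considered statistically significant".

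There is also a descriptive commitment: "For all (re)infections, we will provide exact data on timing of the infection within the first 28 days as well as the pathogen determination".

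No baseline rate, detectable difference or tolerable increase is given for any of these outcomes. The sample size section concerns days on therapy only.

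**The concern.** The bundle starts fewer antibiotic courses, stops some earlier and moves others to oral treatment. For the outcomes that could worsen as a result, the useful question is how large an increase the data can exclude. A test of no difference does not answer that. With few events, a non-significant result cannot distinguish no increase from too little information.

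The article treats its primary outcome differently. There it promises changes in level and trend with 95% CIs and models hospital as a random effect. For the harm outcomes it names neither an effect estimate for the contrast nor any allowance for hospital. Because the results are meant to inform practice and policy recommendations, a bare statement of no significant difference could carry more weight than the data justify.

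**Working it through.** The article gives no power or detectable difference for harm, so there is no figure of its own to reproduce. The check asks what the stated test can detect at the article's own volumes.

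**Inputs from the article**
- 11 hospitals (study setting) and about 2500 births per hospital per year, range 1000–3500 (sample size section): 11 × 2500 = 27,500 births per 12-month period; range 11,000 to 38,500.
- Antibiotic initiation 3.8% before and a target of 2% after (sample size section): 27,500 × 0.038 = 1,045 and 27,500 × 0.02 = 550 treated neonates.
- Fisher test at 0.05. Sidedness is not stated; two-sided is taken.

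**Assumed, because the article does not give them:** baseline rates of 0.1 to 1.0 per 1000 births, or 0.5% to 3% of treated neonates. The second scale matters because health-record data are sampled only from neonates started on antibiotics.

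**Method.** Exact power = Σ Bin(x₁; n₁, p₁) × Bin(x₂; n₂, p₂), summed over all pairs (x₁, x₂) whose two-sided Fisher p-value is below 0.05, with p₂ = 2p₁ or 1.5p₁.

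| Denominator | Baseline | Power, doubling | Power, 1.5-fold |
|---|---|---|---|
| 27,500 v 27,500 births | 0.1 per 1000 | 8% | 3% |
| | 0.3 per 1000 | 31% | 10% |
| | 0.5 per 1000 | 52% | 17% |
| | 1.0 per 1000 | 84% | 34% |
| 1,045 v 550 treated | 0.5% | 16% | 7% |
| | 1% | 33% | 13% |
| | 2% | 60% | 22% |
| | 3% | 79% | 32% |

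**Where power for a doubling crosses 50%.** A normal approximation gives 0.42 per 1000 births and 1.4% of treated neonates. The exact Fisher test gives about 0.48 per 1000 and 1.6%. Hence roughly 0.4–0.5 per 1000 and 1.4–1.6%.

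**Sensitivity to volume (normal approximation).** The births threshold is about 1.05 per 1000 with 11,000 births per period and about 0.30 with 38,500. If the number treated did not fall (1,045 v 1,045), the treated threshold would be about 1.1%. At a 5% baseline with 1,045 v 550, power for a doubling is about 95%.

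**A 1.5-fold rise.** The highest power in the last column is 34%, so it is missed at least 100 − 34 = 66% of the time throughout.

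**What an interval would show.** At 0.5 per 1000, 27,500 births give about 14 events. With 14 events in each period, the rate ratio is 1 with 95% CI exp(±1.96 × √(1/14 + 1/14)) = 0.48 to 2.10. The test reports only no significant difference; the interval shows that a doubling is not excluded.

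These figures ignore clustering by hospital, which would usually lower power.

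**The case against.** The strongest objection is that the article never claims safety. Its aims are antibiotic exposure, additional clinical outcomes and implementation outcomes; it presents safety as established by earlier studies of the interventions; and it states that lack of randomisation limits causal conclusions. A reader might infer that a non-significant harm test will be declared evidence of safety. The text does not say so. This stands: the point is about what the named analysis can show, not about a false statement in the article.

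A reader might also infer that harm is judged by p-values alone. That is too strong, since percentages with 95% CIs where relevant and case-level timing and pathogen data for (re)infections are planned. However, the sentence on CIs attaches them to the percentages, and a case listing does not bound an increase. Neither supplies an interval for the pre/post contrast.

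A third tempting reading is that a doubling of any of the four outcomes would usually be missed. The table contradicts this for the more frequent outcomes, and every baseline rate is an assumption.

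Two further objections stand and shape the fix. Culture-proven EOS is only partly a harm outcome. The primary analysis treats positive blood cultures as a confounder, and the adapted calculator replaces one blood-culture recommendation with observation only, so the rate also reflects case mix and culture practice. And if initiation falls, the treated neonates differ in composition between periods, so a formal margin applied to them could license a stronger claim than the data allow. A missing margin is therefore not an error.

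One could finally say that effect-measure intervals belong in a statistical analysis plan not shown here. But the article does fix the comparison for these outcomes, and the comparison it fixes is the test.

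**Conclusion.** The point holds in limited form. The stated pre/post comparison for the harm outcomes is uninformative when events are few, and no estimate or interval for the contrast is named. A doubling is missed about half the time or more only for the rarest outcomes, below roughly 0.4–0.5 per 1000 births or 1.4–1.6% of treated neonates; at 1.0 per 1000 or 3%, power is about 80% or more. A 1.5-fold rise is missed at least 66% of the time at every baseline examined (0.1–1.0 per 1000 births; 0.5–3% of treated neonates).

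This rests on assumed baseline rates, 2500 births per hospital per year, the 2% initiation target being met, a two-sided test and no clustering. It does not show that the investigators will misread their results. It is a cheap improvement that changes what the study can say about harm.

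**What to change.** In the analysis section for secondary outcomes, for (re)infection, readmission and infection-related mortality, and with an explicit caution for culture-proven EOS:

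- Report the pre/post rate difference and rate ratio with 95% CIs, exact or profile likelihood, allowing for hospital.
- State the denominator for each outcome, live births or treated neonates, and note that the mix of treated neonates changes if initiation falls.
- Say that a non-significant test will not be read as absence of harm, and will be reported with the largest increase not excluded.
- A pre-set margin is optional. It is needed only if the investigators intend to claim no increase in harm, and should then be fixed before the post-implementation data are extracted.

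The cost is analysis wording, with no extra data. The downside is that some harm results will have to be called inconclusive. If a margin is chosen, it also needs baseline rates and clinical agreement that the article does not supply.
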